### Adverse events

Adverse events (AEs) will be queried from the medical record at the end of the intervention phase and between study days 5–7. We will limit the time period for the determination of AEs because we are unaware of any biologically plausible reason to anticipate that either fluid type should lead to AEs remote from the immediate intervention period. AEs that are unexpected, serious, and at least possibly related to study fluid type will be reviewed by the international steering committee and reported promptly to regulatory bodies.

### Sample size

A baseline incidence of MAKE30 in children with septic shock predominantly resuscitated with 0.9% saline was determined based on a prior pediatric study (9.6% MAKE30) [39], the proportion of patients aged 18–21 years enrolled in the SMART trial (9.7% MAKE30) [17], and institutional registry data from two US study sites (5.0% and 7.8% MAKE30). We anticipate a conservative MAKE30 incidence of 6% among children treated in an ED for suspected septic shock largely resuscitated with 0.9% saline. Enrollment of 8800 total participants will provide 95% power to detect an absolute risk reduction (ARR) in MAKE30 from 6.0% for children treated with 0.9% saline to 4.3% for balanced/buffered fluids with a standard type I error of 0.05. This ARR corresponds to the 28% relative risk reduction in MAKE30 observed in the youngest subset of patients (18–21 years) enrolled in SMART. Due to the small anticipated ARR with potential for type II error, we purposely selected a high power of 95% for the primary endpoint. This sample size will also provide 84% power to detect a decrease in mortality from 3% with saline to 2% with balanced/buffered fluids and > 99% power to detect a 1-day reduction in hospital-free days.

Recruitment of this large sample size requires collaboration across > 40 sites from three research networks. Based on the enrollment of 85% of eligible patients in our pilot study [25], sites are anticipated to enroll > 80% of eligible patients. Recruitment will be monitored, with targeted support provided to sites that consistently fall below this target. Targeted support will include local investigators meeting with the lead investigators from their respective networks to review the process for screening, determination of eligibility criteria, education of local emergency clinicians who assess for eligibility, location of enrollment materials relative to patient care in the emergency department, and tracking of reasons for missed enrollments. If enrollment fails to demonstrate improvement toward or above the > 80% target despite these efforts, the site will be considered for removal from study participation and a replacement site will be identified.

### Data/safety monitoring and interim analysis

The study will be monitored by a Data Safety Monitoring Board (DSMB) comprised of 10 international members. Interim monitoring for the superiority of one treatment approach will be performed after enrollment of 15%, 40%, and 70% of total study participants. The significance levels at each interim analysis for the difference in MAKE30 between groups are 0.000000014, 0.00079, and 0.014, respectively, using the symmetric two-sided O’Brien-Fleming boundaries. The DSMB may also consider early termination of the trial if there is evidence of futility using an informal, conditional power approach [41].

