### Statistical analysis

The primary outcome of MAKE30 will be reported using the Mantel-Haenszel (MH) relative risk, stratified by the study site. The primary analysis will be performed using the intention-to-treat (ITT) principle, including all randomized participants for whom the three components of the MAKE30 outcome are not missing, regardless of whether study fluid was administered. To account for the three planned interim analyses, the final analysis will use a significance level of 0.044 for the primary outcome of MAKE30.

Secondary outcomes will also be analyzed using the ITT approach incorporating methods of Benjamini and Hochberg to control for multiple analyses [42, 43]. The analysis plan for secondary outcomes is described in Additional file 4.

A per-protocol analysis will include all participants who receive at least 75% of total crystalloid fluid volume (bolus and maintenance) during the intervention window as the fluid to which the participant was randomized. Because the study intervention (fluid type) is available outside of the study, participants who continue to receive the same fluid to which they were randomized after withdrawal from the study protocol will remain eligible for the per-protocol analysis if they meet the ≥75% threshold. Participants who are found to have been ineligible for enrollment (e.g., age incorrect at initial eligibility assessment) or who receive no crystalloid fluid after randomization will be excluded from the per-protocol analysis. To account for potential confounding introduced into the per-protocol analysis, we will use generalized mixed effect regression models to adjust for known covariate imbalances. We will also conduct an analysis using instrumental variables to adjust for potential bias created by treatment contamination [44].

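### The three interim significance levels and the final level of 0.044 do not come from one O'Brien-Fleming boundary at the planned looks; the mismatch is slightly conservative but should be reconciled

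*Protocol article*

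**What the plan says.** All statements are in the protocol article.

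- **Data/safety monitoring and interim analysis**, timing: "Interim monitoring for the superiority of one treatment approach will be performed after enrollment of 15%, 40%, and 70% of total study participants".
- The same section, thresholds: "The significance levels at each interim analysis for the difference in MAKE30 between groups are 0.000000014, 0.00079, and 0.014, respectively", obtained "using the symmetric two-sided O’Brien-Fleming boundaries". It does not say whether this means the classical boundary or a spending function of O'Brien-Fleming type.
- **Statistical analysis**: because of the three interim looks, "the final analysis will use a significance level of 0.044 for the primary outcome of MAKE30".
- **Sample size**: the primary comparison is planned "with a standard type I error of 0.05", with 8800 participants and 95% power for 6.0% versus 4.3%. The same section claims more than 99% "power to detect a 1-day reduction in hospital-free days". Table 2 defines that outcome as days alive and outside hospital up to day 28.

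**The concern.** Four levels are fixed for one test of one outcome, so they should all belong to one boundary. The classical O'Brien-Fleming boundary and the Lan-DeMets spending function of O'Brien-Fleming type share a name and look alike, but they give different nominal levels, above all at early looks. The article names only O'Brien-Fleming, and its numbers point to one form for the interim looks and to the other for the final analysis.

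At stake are the decision thresholds for MAKE30. The choice of form also has a practical side: a spending function allows the levels to be recomputed if a look does not fall exactly at 15%, 40% or 70%, whereas classical levels are tied to the planned looks. If the discrepancy is noticed only after unblinded results are known, no correction will be credible.

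**Working it through.** **Inputs.** Looks at t = 0.15, 0.40, 0.70 and 1 (Data/safety monitoring and interim analysis). Overall two-sided alpha 0.05 (Sample size). Stated levels 0.000000014, 0.00079, 0.014 (interim) and 0.044 (final). 4400 per arm, from 8800 allocated in equal numbers. Assumption: the information fraction equals the enrolment fraction.

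**Method.** Under the null hypothesis, Z(t)·√t behaves as Brownian motion. The probability of first crossing ±z_k at each look was obtained by recursive numerical integration.

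**Step 1. Lan-DeMets O'Brien-Fleming-type spending, 0.025 per side.** Cumulative two-sided alpha is α(t) = 4·[1 − Φ(2.2414/√t)], where 2.2414 is the upper 0.0125 point of the normal distribution.
- α(0.15) = 0.0000000143; α(0.40) = 0.000788; α(0.70) = 0.01477; α(1) = 0.05.
- Solving for the boundary gives z = 5.670, 3.357, 2.445 and 2.001.

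**Step 2. Classical O'Brien-Fleming, z_k = C/√t_k.** The constant that gives 0.05 overall is C = 2.0114, so z = 5.193, 3.180, 2.404 and 2.011.

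**Step 3. Nominal two-sided levels side by side.**

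| Look | Stated | Lan-DeMets | Classical |
|---|---|---|---|
| 15% | 0.000000014 | 0.0000000143 | 0.00000021 |
| 40% | 0.00079 | 0.00079 | 0.0015 |
| 70% | 0.014 | 0.0145 | 0.0162 |
| Final | 0.044 | 0.0454 | 0.0443 |

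The first two stated levels reproduce under spending to the printed digits; the classical value at 15% is about 15 times larger (0.000000207/0.000000014). The stated 0.014 is either the spending level 0.0145036 truncated, or the alpha spent at that look, 0.01477 − 0.00079 = 0.01398. The stated 0.044 reproduces only in the classical column.

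**Step 4. Other explanations tried.**
- The spending function taken once at 0.05 instead of 0.025 per side: 0.00000042, 0.0019, 0.0184, final 0.0428. No match.
- Lan-DeMets with looks at 25%, 50% and 75%: final 0.0440, but interim levels 0.000015, 0.0030 and 0.018.
- Lan-DeMets with the third look moved to 75%: final 0.0442, but third level 0.019.

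None of these gives all four values.

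**Step 5. Type I error of the stated set.** First-crossing probabilities at the four looks are 0.000000014, 0.00079, 0.01348 and 0.03417. Their total is 0.0484, or 0.0477 to 0.0491 over the rounding of the stated levels. Keeping the stated interim levels, the final level that would use exactly 0.05 is 0.0457.

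**Step 6. Power for 6.0% versus 4.3%.** Drift = 0.017/√[(0.06·0.94 + 0.043·0.957)/4400] = 3.610. Group-sequential power is 94.66% with the stated levels and 94.81% with the Lan-DeMets set, a difference of about 0.15 percentage points. A fixed-sample test at 0.05 has 95.0%, which reproduces the plan's own figure.

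**Hospital-free days.** By the Table 2 definition more days are better, and the trial's hypothesis is that balanced/buffered fluids improve outcomes. The hypothesised benefit is therefore an increase, not a reduction.

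**The case against.** The strongest reply is that nothing is at risk. The stated levels hold the overall error below 0.05, a sponsor may choose a final level slightly stricter than necessary, and the decision changes only for a final p-value in a band about 0.0014 wide (0.0454 − 0.044). The interim levels also fit a common reading of the O'Brien-Fleming name, so the DSMB is not working from an invalid rule. All of this stands, and it limits the point to one of consistency. It does not remove it: the article presents 0.044 as the level that accounts for these interim looks, not as a deliberately stricter choice, and it does not follow from the boundary that produced the interim levels.

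Three stronger readings are tempting and are not supported.

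- A reader might infer that the levels are wrong because they do not add up to 0.05. Their plain sum is 0.0588, but nominal levels at correlated looks are not meant to add up to alpha. The relevant quantity is the overall crossing probability, 0.0484.
- A reader might infer that the 84% power for mortality is wrong because secondary outcomes are analysed "incorporating methods of Benjamini and Hochberg to control for multiple analyses". The 84% reproduces as the power of a single test (83.9% at 0.044, 85.2% at 0.05), and the article never calls it multiplicity-adjusted. Benjamini-Hochberg has no fixed per-test level, and the secondary analysis plan is in Additional file 4, which is not at hand.
- A reader might take the hospital-free-days wording as a power error. A two-sided test has the same power in either direction, so no number changes.

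**Conclusion.** The four stated levels are not one O'Brien-Fleming boundary for looks at 15%, 40% and 70%. The interim levels follow Lan-DeMets spending; the final level belongs elsewhere, probably to the classical boundary, though that origin is an inference because another look schedule also yields 0.044. The overall two-sided type I error is about 0.0484, so error is controlled and the mismatch is slightly conservative. The practical effect is confined to a final p-value between 0.044 and about 0.045, which would be declared non-significant although alpha remains.

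These results assume that information accrues in proportion to enrolment and that the looks fall exactly as planned. The hospital-free-days phrase is a separate wording slip without numerical consequence.

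**What to change.** Name one construction and give all four levels from it. Two coherent choices for the planned looks are:

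- Lan-DeMets O'Brien-Fleming-type spending: 0.000000014, 0.00079, 0.0145 and final 0.045 (0.0454 before rounding), recomputed at the actual information fractions; or
- classical O'Brien-Fleming: 0.00000021, 0.0015, 0.016 and final 0.044.

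The first keeps the first two interim levels unchanged and allows for looks that drift from plan. Bring the DSMB documents into line, and make the change before unblinded results can influence it. In the Sample size section, change the hospital-free-days effect to a 1-day increase.

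The cost is wording and an update of the DSMB documents. The sample size does not change, and power for the primary outcome moves by about 0.15 percentage points at most.

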### Statistical analysis

The primary outcome of MAKE30 will be reported using the Mantel-Haenszel (MH) relative risk, stratified by the study site. The primary analysis will be performed using the intention-to-treat (ITT) principle, including all randomized participants for whom the three components of the MAKE30 outcome are not missing, regardless of whether study fluid was administered. To account for the three planned interim analyses, the final analysis will use a significance level of 0.044 for the primary outcome of MAKE30.

Secondary outcomes will also be analyzed using the ITT approach incorporating methods of Benjamini and Hochberg to control for multiple analyses [42, 43]. The analysis plan for secondary outcomes is described in Additional file 4.

A per-protocol analysis will include all participants who receive at least 75% of total crystalloid fluid volume (bolus and maintenance) during the intervention window as the fluid to which the participant was randomized. Because the study intervention (fluid type) is available outside of the study, participants who continue to receive the same fluid to which they were randomized after withdrawal from the study protocol will remain eligible for the per-protocol analysis if they meet the ≥75% threshold. Participants who are found to have been ineligible for enrollment (e.g., age incorrect at initial eligibility assessment) or who receive no crystalloid fluid after randomization will be excluded from the per-protocol analysis. To account for potential confounding introduced into the per-protocol analysis, we will use generalized mixed effect regression models to adjust for known covariate imbalances. We will also conduct an analysis using instrumental variables to adjust for potential bias created by treatment contamination [44].

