### Outcomes

The primary outcome will be MAKE30—a composite of death from any cause, initiation of RRT, or persistent kidney dysfunction—at either 30 days following study enrollment or hospital discharge, whichever comes first (Table 2) [38]. RRT will include treatment (or attempt to treat if the participant does not tolerate treatment) with any renal replacement modality during the hospitalization that was not a continuation of pre-hospital chronic therapy, censored at 30 days after randomization. Persistent kidney dysfunction will be measured as final creatinine ≥200% of baseline (i.e., at least a doubling of baseline creatinine) *and* a minimum absolute increase of ≥0.3 mg/dL. Baseline serum creatinine will be recorded as the lowest creatinine available between 12 months and 24 h prior to enrollment or, for participants without such data, an imputed value using established median values for age and sex [39]. Secondary efficacy, safety, and biologic outcomes are listed in Table 2.

**Table 2 Tab2:** Study outcomes

Outcome	Definition
Primary outcome	
MAKE30 (primary outcome)	Major adverse kidney events at 30 days (defined as at least one of the following): • Death • New renal replacement therapy • Persistent kidney dysfunction at hospital discharge or 30 days (serum creatinine ≥2x baseline or median value for age if no baseline available *and* a minimum absolute increase of ≥0.3 mg/dL)
Secondary effectiveness outcomes	
Death	All-cause mortality at hospital discharge, 28 days, and 90 days^b^
Hospital length of stay	Days from hospital admission until discharge, censored at 90 days
Hospital-free days out of 28 days	Days between enrollment and day 28 in which patient was alive and out of the hospital
New inpatient renal replacement therapy	New continuous renal replacement therapy, hemodialysis, or peritoneal dialysis
Persistent kidney dysfunction at hospital discharge	Serum creatinine ≥2x baseline or median value for age if no baseline^a^ available, censored at 30 days
Secondary safety outcomes^c^	
Hyperlactatemia	> 4 mMol/L
Hyperkalemia	> 6 mEq/L
Hypercalcemia	Ionized calcium > 1.35 mmol/L or total serum calcium > 12 mg/dL
Hypernatremia	> 155 mEq/L
Hyponatremia	< 128 mEq/L
Hyperchloremia	> 110 mEq/L
Thrombosis	Therapy for new arterial or venous thrombus with systemic anticoagulant OR Clotting of intravenous catheter in subjects receiving ceftriaxone and lactated Ringer’s

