### Missing Data

The primary ITT analysis will use complete case data if the percentage missing the primary outcome is ≤5% of total enrollment *and* all three country-specific percentages missing the primary outcome is ≤7% of country-specific enrollment. If these criteria are not met, we will use multiple imputation for the primary analysis with data assumed to be missing at random unless available data contradict this assumption. If the primary outcome is missing from between 1% and 5% of total participants, we will perform an adjunctive analysis using multiple imputation in addition to the complete case analysis. In addition, we will examine differences between participants with and without missing data and conduct a sensitivity analysis using the inverse-probability-weighting (IPW) method to conduct multiple imputation for the missing data [46, 47]. New analyses performed in addition to those described above will be delimitated as *post hoc* and considered hypothesis-generating.

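### The primary analysis set requires all three MAKE30 components to be non-missing, although one known component already settles the outcome, so a known death or new RRT without a final creatinine would be excluded

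*Protocol article*

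**What the plan says.** Three parts of the protocol article bear on this point.

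- **Outcomes, Table 2** defines the composite as "Major adverse kidney events at 30 days (defined as at least one of the following": death, new RRT, or persistent kidney dysfunction at discharge or 30 days. The text above the table adds, for the third component, "Persistent kidney dysfunction will be measured as final creatinine ≥200% of baseline", together with a minimum absolute rise. It gives no rule for a child who died or received RRT and has no such value.
- **Statistical analysis** restricts the primary analysis to a set "including all randomized participants for whom the three components of the MAKE30 outcome are not missing, regardless of whether study fluid was administered".
- **Missing Data** says the primary analysis "will use complete case data if the percentage missing the primary outcome is ≤5% of total enrollment", with a second condition of at most 7% in each country. If either condition fails, multiple imputation becomes the primary analysis. It also says: "If the primary outcome is missing from between 1% and 5% of total participants, we will perform an adjunctive analysis using multiple imputation". These triggers refer to the primary outcome being missing, not to a component being missing.

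**The concern.** Under Table 2 a death or a new course of RRT makes the child a MAKE30 event whatever the creatinine shows. The analysis-set sentence asks for more: none of the three components may be missing. A child who dies very early, before any usable creatinine is recorded, fails that condition. In the complete-case branch the child is removed from both numerator and denominator. In the imputation branch a known event is replaced by a guess.

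The children at risk of removal are all events, so the rule lowers both event rates and costs power. The trial is open-label and laboratory data come from the medical record. If the chance of having a creatinine before death differed between arms, the relative risk would also be biased. The rule decides who counts in the primary endpoint, so changing it after outcome data have been seen would be hard to defend.

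**Working it through.** **Inputs from the article.** 8,800 participants allocated equally, so 4,400 per arm; MAKE30 6.0% with saline and 4.3% with balanced fluid; mortality 3% and 2% (all from Sample size and Randomization); final significance level 0.044 (Statistical analysis).

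**Assumptions.** The share *f* of deaths with no final creatinine is not given, so a range is shown. The 3% and 2% mortality figures are taken as deaths within the MAKE30 window. Tests are two-sided. The article gives no RRT rate, so RRT cases are not modelled.

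**Step 1: the plan's own figure.** The article states: "Enrollment of 8800 total participants will provide 95% power to detect an absolute risk reduction (ARR) in MAKE30" from 6.0% to 4.3%. Use power = Φ[(|p₁ − p₂| − z·SE₀)/SE₁], with SE₀ from the pooled proportion and SE₁ from the separate proportions.

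- Pooled proportion = (0.060 + 0.043)/2 = 0.0515
- SE₀ = √(0.0515 × 0.9485 × 2/4400) = 0.004712
- SE₁ = √[(0.060 × 0.940 + 0.043 × 0.957)/4400] = 0.004709
- At 0.05: (0.017 − 1.960 × 0.004712)/0.004709 = 1.649, power 95.0%. The stated figure reproduces.
- At 0.044: (0.017 − 2.014 × 0.004712)/0.004709 = 1.595, power 94.5%

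**Step 2: how much of the endpoint is death.** Expected events are 4400 × 0.060 = 264 and 4400 × 0.043 = 189.2. Expected deaths are 4400 × 0.03 = 132 and 4400 × 0.02 = 88, together 220.

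**Step 3: remove a share *f* of deaths, equal in both arms.**

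- Saline rate = (264 − 132*f*)/(4400 − 132*f*)
- Balanced rate = (189.2 − 88*f*)/(4400 − 88*f*)

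Power uses the Step 1 formula with the reduced group sizes at 0.044.

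| *f* | Events lost | % of 8,800 | Saline | Balanced | RR | Power |
|---|---|---|---|---|---|---|
| 0 | 0 | 0 | 6.00% | 4.30% | 0.72 | 94.5% |
| 5% | 11 | 0.13% | 5.86% | 4.20% | 0.72 | 93.8% |
| 10% | 22 | 0.25% | 5.72% | 4.11% | 0.72 | 93.0% |
| 25% | 55 | 0.63% | 5.29% | 3.82% | 0.72 | 90.1% |
| 50% | 110 | 1.25% | 4.57% | 3.33% | 0.73 | 82.7% |
| 100% (bound) | 220 | 2.50% | 3.09% | 2.35% | 0.76 | 54.4% |

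**Step 4: unequal shares, no true effect.** Set MAKE30 at 6% and mortality at 3% in both arms, with *f* = 10% for saline and 20% for balanced fluid.

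- Saline: (0.060 − 0.003)/(1 − 0.003) = 5.72%
- Balanced: (0.060 − 0.006)/(1 − 0.006) = 5.43%
- RR = 5.43/5.72 = 0.95

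**Step 5: would the missing-data triggers catch it?** Even if every expected death were dropped, 220/8800 = 2.5%, below the 5% overall limit. These cases alone would not make imputation the primary analysis on that criterion. Below 1% (88 children), the adjunctive imputation is not required either.

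**The case against.** The strongest reply is that the sentence is loosely worded and the intention is sound. The Missing Data section sets its thresholds on the primary outcome being missing, and under Table 2 a known death settles that outcome. Read together, the authors may have meant only that MAKE30 can be determined. That is plausible, but the analysis-set sentence names the three components and nothing in the article overrides it.

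The second reply concerns size, and it largely stands. The article asks for a final creatinine without requiring a discharge or day-30 sample. If the last in-hospital value counts, a child who died lacks the component only when no usable value exists. The affected group is then small and the upper rows of the table are the relevant ones. With equal loss in both arms, the primary measure, a relative risk, barely moves. Nothing in the article suggests that creatinine is obtained at different rates by arm, so the 0.95 is an illustration and not a forecast.

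Third, deaths would not vanish from the report. All-cause mortality is a separate secondary outcome, and all outcomes are reported by group. That limits the harm to interpretation but does not repair the primary endpoint.

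A reader might also infer that the missing-data plan as a whole is unsound, because it leans on missing at random and describes inverse-probability weighting as a way to impute. The article does not support that. It makes the assumption conditional on the available data, it plans to compare participants with and without missing data, and weighting can be combined with imputation. Further sensitivity analyses are matters for a statistical analysis plan that is not shown.

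**Conclusion.** The conflict between the analysis-set sentence and Table 2 is real and sits in the definition of the primary analysis. Followed as written, the rule discards or imputes outcomes that are already known, and the missingness thresholds would not reveal it.

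The likely numerical effect is modest. For assumed shares of 5% to 50% of deaths without a creatinine, power at 0.044 is 93.8% to 82.7% against 94.5%, and the relative risk is 0.72 to 0.73 if loss is equal across arms. Bias arises only if loss differs by arm. All of this rests on a share that the article does not give.

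Two stronger readings should be resisted. One is that the trial will lose a large part of its deaths: the 54.4% power is a bound with every death removed, not an expectation. The other is to set the 5% tolerance (440 children) against the roughly 453 expected events as a measure of this problem. The 440 is the general allowance for missing outcomes; this defect involves at most 220 deaths plus an unknown number of RRT cases. No stated figure in the article is wrong.

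**What to change.** Replace the three-component condition with a scoring rule for MAKE30:

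- **Yes** if any component is known to be present.
- **No** if all three are known to be absent.
- **Missing** only if no component is known to be present and at least one is unknown.

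Apply the 5% overall, 7% country-specific and 1% to 5% triggers in the Missing Data section to outcomes that are missing under this rule. Settle this before outcome data are analysed.

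The cost is one sentence and a little programming. No new data are needed. No known event is lost, so the expected counts return to 264 and 189, power stays at 95.0% at 0.05 and 94.5% at 0.044, and the sample size is unchanged.
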